**12) Procedures Involved:**

**Data collection:** The existing UC Davis Transfer Center Children's Requests records in EPIC will be used to identify patients meeting the entrance criteria from participating hospital EDs. Qualifying patient encounters will be documented by date, hospital name, patient name and patient date of birth in a password protected excel database and stored on secure, password protected, encrypted University of California computers. The UC Davis project manager will then send requests for corresponding medical charts for qualifying patient encounters to the associated participating hospital sites via a hospital-specific password protected excel database through secure email or secure fax with the date of encounter, patient name, and patient date of birth. There will not be any other information or patient identifiers on this spreadsheet. Each remote site PI will sign an agreement attesting that they will not re-use or re-disclose those PHIs to any other person or entity.

Medical records will be copied by remote site personnel and de-identified of all patient and hospital identifications. These de-identified medical records will be used to abstract the necessary data to accomplish the objectives of this proposal. The investigators cannot ascertain the identity of the subjects.

The medical charts will be copied at the remote site and no additional data will be collected at University of California Davis Health System (UCDHS). The data is provided to the Principal Investigator after being de-identified, as the method of reporting is a case report form or a medical record that has been both blacked-out of identifiable information and re-copied.

The de-identified charts will be scanned and securely uploaded into REDCap. REDCap is a secure, encrypted, password protected research database available at UC Davis. The charts will then be reviewed to obtain data for our four outcomes: physician experts will review and score the de-identified medical records as to the quality of care using a previously validated instrument; we will determine from the record the patient disposition; pharmacy experts will review and score the de-identified medical records as to the number of medication errors; knowing the disposition of care, we will determine the costs based on standardized average transfer-hospital admission charges. We are therefore collecting several data points: patient disposition, medication errors, and diagnosis.

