We will use a novel cluster randomized unbalanced crossover trial design. The first year of the project will be a "ramp-up" period during which the protocol will be re-reviewed during a site visit to the participating EDs and random block assignments will be generated and delivered. The last year will be reserved for data analysis, study closeout, and manuscript preparation. The intermediate 2-year period will be divided into 4 six-month calendar time periods for carrying out the protocol and data collection. For each 6-month period, each ED will have a randomized treatment assignment for pediatric emergency and critical care consultations ("M" for telemedicine and "P" for telephone.) Participating EDs (the unit of randomization) will be stratified into two strata by size of ED and geographical location. EDs

will then be randomized within-strata to one of the four unbalanced (3:1) crossover treatment assignment sequences, each consisting of a 6-month period: PMMM, MPMM, MPPM, or MMMP. During these assigned periods, the type of consultation being assigned will be **strongly encouraged**, but deviating from protocol (i.e., using telephone consultation when randomized to telemedicine, or vice-versa) will be allowed as needed by the physicians. If a protocol arm deviation occurs, then notes explaining the circumstances must be documented. As telephone consultations remain the current standard of care, we anticipate our intervention to be primarily the encouragement of the use of telemedicine (as opposed to the encouragement of the use of telephone).

Regarding randomization, patients will receive the care that is most appropriate for them. The study will not be a true randomization, because the physicians will determine whether or not to use the telephone or telemedicine for the consultation. While we will encourage one modality over the other at different periods of time, the decision is always up to the treating physicians. Therefore, the risk will be minimized for patients.

We will abstract the following variables from eligible patient medical records:

- Demographic information (age, race, gender, insurance type)
- Specialist consultation data (whether a specialist consult was obtained: Yes/No; and if so, which type: Telephone, Telemedicine)
- The variables required for the Pediatric Risk of Admission (PRISA II)
- The variables required for the Pediatric Emergency Assessment Tool (RePEAT)

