**14) Data Management and Confidentiality:** The existing UC Davis Transfer Center Children's Requests records in EPIC will be used to identify patients meeting the entrance criteria described above from participating hospital EDs during the study period. The Transfer Center Children's Requests records are existing hospital records in EPIC that track all children-specific requests for consultation or transfer to UC Davis from outside hospitals and clinics. Qualifying patient encounters will be identified and documented by date, hospital name, patient name and patient date of birth in a password protected excel database and stored on secure, password protected, encrypted University of California computers. The UC Davis project manager will then send requests for corresponding medical charts for qualifying patient encounters to the associated participating hospital personnel via a hospital-specific password protected excel database through secure email or secure fax with the date of encounter, patient name, and date of birth. There will not be any other information or identifying information on this spreadsheet.

Once qualifying patient encounters are identified, medical charts will be copied and de-identified by remote hospital site personnel. All data collected from each of the participating hospitals will be collected confidentially so that no patient identifiers or links to patient and hospital identifiers will be contained in the research records. This

will be accomplished by “blacking out” all patient and hospital identifiers permanently with a black marker by remote site personnel photocopying the medical records. A unique identification number will be assigned to each of a patient’s data. Each site will be responsible for holding the key with the unique identifier and is prohibited from releasing the key to the study investigators under any circumstance.

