The blacked-out copies will be re-copied to ensure that text cannot be read through the marker. These de-identified, re-copied medical records will be either collected in-person by the study personnel or will be sent to the study investigator by certified mail. These copied medical records (without patient or hospital identifiers) will be used to fulfill the objectives of the grant. The same de-identified medical records will be used to obtain the data necessary for quality of care, severity of illness measures, medication errors, and patient disposition. Since existing records will be used and all patient and hospital identifiers will be eliminated, there are no anticipated risks to subjects whose records will be reviewed.

All the medical records included in the analyses will be photocopied at the remote sites. These records will be de-identified prior to leaving the Medical Records Department at the participating institutions. The de-identified medical record will be stored in a locked office which resides in a secured building within UC Davis Children’s Hospital. All of the data that pertains to the patient and data for quality measures will be abstracted from the de-identified medical record and entered into a secure password-protected database on a single password-protected personal desktop computer in a locked office at UC Davis Children’s Hospital. All study personnel will be trained through an in-person training session before the start of the project on the data abstraction, collection and data entry process. All data will be managed, cleaned, and analyzed at UC Davis Children’s Hospital. All study personnel, software, computers and research resources required to conduct this study will be supported from this grant except for the pediatric subspecialist. The investigators and staff are fully committed to the security and confidentiality of all data collected from the participating hospitals. All study personnel involved in this proposed project have received Human Subjects Protection and HIPAA education.

The data from this program will be shared with only statistical consultants and an economist, who will ensure that the data also be on a single password-protected desktop computer in a locked office in a secured building.

**15) Provisions to Monitor the Data to Ensure the Safety of Subjects:** Research does not involve more than Minimal Risk to subjects.

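### As written, the quality and medication-error scorers can be expected to see whether the consultation was by telemedicine or telephone, because redaction covers identifiers only and no masking step is described.

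*Protocol*

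**What the plan says.** The path of a chart can be followed through sections 12 and 14 of the protocol.

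- **Redaction.** Section 12 (Data collection): "Medical records will be copied by remote site personnel and de-identified of all patient and hospital identifications". Section 14 says that confidentiality is achieved by blacking out "all patient and hospital identifiers permanently with a black marker by remote site personnel photocopying the medical records". Consultation type is not among the items to be removed, and confidentiality is the only purpose given for redaction.
- **Abstraction of modality.** Section 12: "We will abstract the following variables from eligible patient medical records", followed by a list that includes "Specialist consultation data (whether a specialist consult was obtained: Yes/No; and if so, which type: Telephone, Telemedicine". Section 12 also says that nothing further is collected at the coordinating health system.
- **Scoring.** Section 12: "physician experts will review and score the de-identified medical records as to the quality of care using a previously validated instrument", and "pharmacy experts will review and score the de-identified medical records as to the number of medication errors".
- **One set of records.** Section 14: "The same de-identified medical records will be used to obtain the data necessary for quality of care, severity of illness measures, medication errors"; disposition comes from them too.

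Under Outcome Measures, the quality score is an implicit review: five items, one of them a rating of overall quality, summed for each reviewer. Medication errors are assessed with a previously published instrument. For both outcomes the stated hypothesis favours telemedicine. The protocol nowhere describes masking of reviewers to modality, assigned period or hypothesis.

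**The concern.** An implicit review asks an expert for a judgement of the care. If the chart shows that a specialist took part by video rather than by telephone, the reviewer's opinion of video consultation can enter the score. Such a preference moves exactly with the modality received, so analysis of the scores alone cannot separate it from a real effect on care. Quality of care is the first aim, and an apparent benefit could be partly or wholly a reviewer effect.

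How much of the preference reaches the result depends on the comparison. By randomised period, it is diluted by the difference in telemedicine uptake between the two kinds of period. By modality received, which is how the study-design text in section 5 describes the groups, it enters in full.

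**Working it through.** **Step 1: is modality legible to the scorers?** No arithmetic applies, so the passages are set side by side.

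1. Consultation type is to be abstracted from the medical record (section 12), so it has to be readable there.
2. The redaction rules (sections 12 and 14) remove patient and hospital identifiers only, so they leave it readable.
3. The same de-identified records are used for quality, severity, medication errors and disposition (section 14), and the experts score those records (section 12).
4. No second redaction and no separate reviewers' copy is described.

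Followed as written, the plan puts modality in front of the scorers.

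**Step 2: does the chart also reveal the randomised period?** Not directly. The hospital is redacted, and the four printed sequences (PMMM, MPMM, MPPM, MMMP) put both kinds of site in every period:

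| Period | M sequences | P sequences |
|---|---|---|
| 1 | 3 | 1 |
| 2 | 2 | 2 |
| 3 | 3 | 1 |
| 4 | 3 | 1 |

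A visit date without the hospital therefore does not identify the assignment. Assignment can be guessed in part from modality. Arm-deviation notes would reveal it if they are kept in the chart; the protocol does not say where they are filed.

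**Step 3: how large could the effect be?** The protocol gives no figure to reproduce. This is an illustration on assumptions.

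- From section 7: 600 consultations, which is a cap.
- From section 12: the sequences as printed contain 11 M and 5 P periods out of 16. With sequences used equally and equal numbers per period, that is 600 × 11/16 = 412.5 charts against 600 × 5/16 = 187.5.
- Assumed: reviewer preference d of 0.1 or 0.2 SD; uptake gap g between M and P periods of 20 or 50 percentage points; independent charts; two-sided 5% test.

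SE = √(1/412.5 + 1/187.5) = 0.088 SD.

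Bias in the by-period difference = d × g.

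Rejection with no true effect = Φ(−1.96 + bias/SE) + Φ(−1.96 − bias/SE).

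| d (SD) | g | Bias (SD) | Bias/SE | False rejection |
|---|---|---|---|---|
| 0.1 | 0.20 | 0.02 | 0.23 | 5.6% |
| 0.2 | 0.20 | 0.04 | 0.45 | 7.4% |
| 0.1 | 0.50 | 0.05 | 0.57 | 8.8% |
| 0.2 | 0.50 | 0.10 | 1.14 | 21% |

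Section 12 also describes the sequences as 3:1, which MPPM is not. A 450:150 split gives SE = √(1/450 + 1/150) = 0.094 SD and about 18.5% in the last row. In a comparison by modality received, the bias is the full d, 0.1 to 0.2 SD.

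**The case against.** **The protocol never says that reviewers are unmasked.** True. It is an inference from the redaction scope, the abstraction list and the shared records. Section 12 also mentions a case report form as an alternative way of reporting, so modality could arrive separately. That weakens the inference but does not remove it: the abstraction list still takes consultation type from the medical record, and no provision takes it out of the scorers' copy.

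**An unseen analysis plan or reviewer manual may deal with it.** What is blacked out at the sites is a matter of conduct, and this protocol fixes it. An analysis plan cannot mask a chart that has already been scored.

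**The scorers may have no stake.** This stands. The protocol calls them only physician and pharmacy experts, and the staff list in section 24 does not name them. A reader might infer that they are investigators who share the hypothesis; the document does not support that. The concern does not need it, since an outside expert can also have a view on video consultation.

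**Medication errors are different.** Largely conceded. Only the quality instrument is called implicit. Error scoring still needs expert judgement, but the exposure is smaller, and the SD-scale illustration was not derived for error counts.

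**The illustration is arbitrary.** Conceded as to size. The preference and the uptake gap are both assumed, 600 is a ceiling, and clustering by ED is ignored. Fewer charts or a larger SE would lower the rejection rates but leave the bias unchanged.

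**Conclusion.** The point holds as a weakness in the procedure as written: the stated redaction leaves modality legible, and the same records go to the people who score a judgement-based first-aim outcome. It is more than a missing detail, because carrying out the written steps produces the exposure. It applies chiefly to aim 1 and less to aim 3. Disposition is less open to it.

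The size is undetermined. The range of about 6% to 21% false rejection at a nominal 5% rests wholly on the assumed 0.1 to 0.2 SD preference, the assumed 20 to 50 point uptake gap, 600 independent charts and the 11:5 split.

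Three stronger readings are tempting, and the document supports none of them:

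- That the protocol declares unmasked assessment. It is silent, and exposure is inferred from the data flow.
- That the trial has a false-positive rate of 21%. That is the top of an assumed range.
- That the chart discloses the randomised period. It shows modality received; with the hospital redacted, the date alone does not give the assignment.

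**What to change.** 1. Record modality under the study ID on a separate form, completed by site staff or by an abstractor who does not score. Linking from the Transfer Center log is not workable under the present rules, because section 14 leaves the key with each site and forbids its release to the investigators.
2. From the copy shown to quality and medication-error reviewers, redact wording that reveals a telemedicine, video or telephone consultation. Keep the clinical content that they need to rate. Charts are scanned into REDCap before review, so the masked copy can be made there. Redacting visit dates is optional.
3. State in the protocol that reviewers are masked to modality and assigned period.
4. Have each reviewer record a guess of the modality for each chart, so that the success of masking can be reported.

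**Cost.** The extra redaction is modest, since every chart is already handled for this purpose, but it is not free. Version 7 is dated 7/5/2017 and enrollment is projected to end on 8/31/2017, so charts already copied would need a second pass. Any already scored from an unmasked copy would need scoring again; the protocol does not say whether there are any. Masking will be imperfect where the narrative gives the modality away, and some consultation content may be lost to the rating.

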**Pediatric Risk of Admission (PRISA II) [ Time Frame: Year 3 ]**

The investigators hypothesize that children receiving care in EDs during randomized periods of telemedicine use will be admitted more appropriately than similar children who receive care during periods randomized to telephone use. To compare the cohort of seriously ill children treated during the telephone and telemedicine time blocks, observed to expected (O/E) ratios will be calculated using an intention-to-treat framework.

**Pediatric Emergency Assessment Tool (Re-PEAT) [ Time Frame: Year 3 ]**

The investigators hypothesize that children receiving care in EDs during randomized periods of telemedicine use will be transferred more appropriately than similar children who receive care during periods randomized to telephone use. The investigators will compare O/E ratios.

**Quality of Care Implicit Review Instrument [ Time Frame: Year 3 ]**

The investigators hypothesize that children receiving care in EDs during periods of telemedicine use will receive higher quality of care than similar children who receive care during periods of telephone use. A previously validated 5-item implicit review instrument that measures 4 aspects of process of care in the ED, along with a fifth item assessing the overall quality of care provided to the patient will be used. The sum of the 5 item-specific scores will be aggregated from each reviewer to obtain a summary quality score for each medical record.

**Medication Error Rate Instrument [ Time Frame: Year 3 ]**

The investigators hypothesize that children receiving care in EDs during periods of telemedicine use will experience fewer physician-related medication errors than similar children who receive care during periods of telephone use. A previously published instrument developed specifically to evaluate medication errors among children receiving care in the ED will be used.

**Economic Efficiency Cost-Analysis [ Time Frame: Year 3 ]**

The investigators hypothesized that care provided to children in EDs during randomized periods of telemedicine use will be economically more efficient than care provided during randomized periods of telephone. Cost analysis will estimate return-on-investment indicating the cost saving amount per \$1 investment in telemedicine compared to care without telemedicine.

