***Our third aim is to determine the effect of tele-emergency care on the frequency of physician-related medication errors.*** Medication errors will be compared between children receiving telemedicine consultations and telephone consultations using retrospective chart review and a previously published instrument developed specifically to evaluate medication errors among children receiving care in the ED.

***Our fourth aim is to determine the economic efficiency of tele-emergency care.*** We will compare the economic efficiency of care provided to children receiving telemedicine consultations and telephone consultations using economic evaluations, including cost analysis and cost-effectiveness analysis. The source of data will be the retrospective collection of the number of consultations using the telephone and telemedicine and estimated of costs of care using previously published data.

- 5) **Background:** Many rural EDs are not experienced in the care of pediatric patients, particularly those children who are seriously ill. A potential remedy for this problem is to provide rural and/or underserved EDs with pediatric subspecialty support for emergencies using telemedicine. While the standard of care is to provide these consultations by telephone, telemedicine (the use of live, interactive, audiovisual teleconferencing) may be a better means of providing these consultations.

***Pediatric critical care telemedicine program at UC Davis:*** The telemedicine program at the University of California, Davis Children's Hospital was one of the first programs to provide telemedicine consultations in emergency and critical care settings for children. As of January 2014, we have conducted more than 200 emergency telemedicine consultations. There are currently 26 hospital EDs in our pediatric tele-emergency network, 16 of which will be participating in this proposed study.

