The Pediatric Emergency and Critical Care Telemedicine Program at UC Davis Children's Hospital has a longstanding ability to provide 24/7 pediatric emergency and critical care consultations using either the telephone or telemedicine to all 26 EDs in the network. The type of consultation obtained (telemedicine or telephone) is currently at the discretion of the receiving ED physician and the consulting pediatric critical care physician. The consultations involve live interactive audiovisual communications from the UC Davis physicians to the patient, referring providers (MD/RN/RT), and the parent/guardians of the patient. Typically, approximately 10% of the children that are most seriously ill (triaged to the highest two categories) receive telemedicine consultations while the vast majority receive only telephone or no consultation.

***Study design:*** This will be a retrospective review of prospective data evaluating different outcomes among children who receive telemedicine consultations versus those who receive telephone consultations. All data that will be collected will be obtained retrospectively from

the de-identified medical records of children presenting to the participating ED that meet the entrance criteria. Ultimately, the use of telemedicine and/or telephone will continue to be up to the discretion of the treating ED physician and the consulting pediatric critical care physician. There will be periods of time where one type of consultation will be encouraged per the study protocol, but patients will continue to receive the most appropriate form of care.

**6) Inclusion and Exclusion Criteria:** The study will include de-identified chart review of children up to 14 years of age presenting to participating EDs who received either a telemedicine or telephone consultation with a UC Davis pediatric or neonatal critical care physician.

**7) Number of Subjects:** Up to 600 total consultations, inclusive, from participating sites.

The overall goal of this project is to evaluate the impact of telemedicine consultations on seriously ill children with regard to several health and economic outcomes. The proposed project will evaluate an existing telemedicine emergency network based out of the UC Davis Children's Hospital in Sacramento, CA. Since its inception, this program has expanded to include 26 EDs, mostly located in rural, underserved Northern California. For the purposes of this study, we will include 16 of the EDs.

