- Disposition data (whether the patient was discharged, admitted or transferred)
- Outcome data for ED (survival, length of stay in ED)
- Outcome data for hospitalized patients (survival, length of stay, ICU utilization)

Phase two of data analyses will include securely sending a subset of our collected de-identified data to the University of Iowa's Rural Telehealth Research Center for further analysis. The Rural Telehealth Research Center at the University of Iowa (UI) was hired by the grant administrators at the Health Resources and Services Administration who has funded this grant effort to six grantees. Each of the grantees are asked to send their de-identified data to UI for analyses to evaluate the impact of tele-emergency programs across the nation. Grantees are asked to submit the following de-identified data variables relevant to the current project:

- ED visit arrival time
- ED exam start time
- ED visit departure time
- ED discharge disposition
- Completion of tele-ED consultation
- Tele-ED consultation start time
- Tele-ED consultation end time
- Tele-ED technical success
- Race

- Sex
- Age (categories include <1, 1-14)
- ICD 10 code
- Reason for visit
- Primary payer
- Billed amount for ED visit

***Economic Evaluation:*** To evaluate the economic efficiency of the tele-emergency network, we will apply standard economic evaluation methods to data collected during the telephone and telemedicine time periods of the randomized block design. Our team has previously conducted similar analyses comparing patients who have received telephone versus telemedicine consultations and our positive findings are currently under peer review at a major medical journal.

Knowing the disposition of the patient, we will assign any of the following costs from external data sources:

1. Cost of ED treatment (this will be the same for all patients): This will be estimated using a National Emergency Department Sample (NEDS).
2. Cost of Hospitalization: This will be estimated using the KID database from the national Healthcare Cost and Utilization Project (HCUP). The average hospital admission costs will be used to estimate hospital admission to a rural, community, and urban hospital for admissions to those hospitals, respectively.
3. Transport costs: If a patient requires transport, we will use previously published estimates for air or ground transportation costs for interfacility transports.

**13) Data and Specimen Banking:** N/A

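### The return per dollar is stated against care with no telemedicine, but the randomised contrast is between two encouragement policies with telemedicine available in both

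*Protocol*

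**What the plan says.** The protocol states the economic comparator in several places and in three ways.

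- **Outcome Measures, Economic Efficiency Cost-Analysis, hypothesis.** Care in randomised telemedicine periods "will be economically more efficient than care provided during randomized periods of telephone".
- **Same outcome, next sentence.** The result is a return on investment, given as the "cost saving amount per \$1 investment in telemedicine compared to care without telemedicine".
- **Section 4, fourth aim.** The aim is to "compare the economic efficiency of care provided to children receiving telemedicine consultations and telephone consultations using economic evaluations". This compares children by the modality they received.
- **Section 12, Economic Evaluation.** On the data source: "we will apply standard economic evaluation methods to data collected during the telephone and telemedicine time periods of the randomized block design".

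Two further statements fix what those periods contain. Section 5 says the programme can give round-the-clock "consultations using either the telephone or telemedicine to all 26 EDs in the network", and the 16 study EDs belong to that network. On departures from the assigned modality, section 12 says "using telephone consultation when randomized to telemedicine, or vice-versa) will be allowed as needed by the physicians". It adds that the treating physicians always decide, and describes the intervention as mainly encouragement to use telemedicine.

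**The concern.** A return per dollar needs a saving and an investment that belong to the same comparison. Here the saving comes from assigned periods in EDs that can use telemedicine in all of them. The label attached to the ratio names a state with no telemedicine, which no ED and no period is designed to provide.

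A hospital or funder would probably read the result as what it gains by acquiring telemedicine. The trial randomises something narrower: encouraging telemedicine rather than telephone where both are on offer. If the label stays, the report will claim a comparison that the randomisation does not support, and the same data could yield quite different ratios depending on how the dollar is defined.

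**Working it through.** The protocol states no return, uptake by period or telemedicine cost, so there is no figure to reproduce. The check has three steps.

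**1. Possible meanings of the comparator**

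| Meaning | Observed in the trial? | Randomised? |
|---|---|---|
| ED without the programme | No: telemedicine is available to all network EDs (section 5) | Not applicable |
| Period assigned to telephone | Yes, but telemedicine is allowed in it (section 12) | Yes |
| Child who received telephone only | Yes: consultation type is abstracted (section 12) | No: physicians choose |

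No row is both free of telemedicine by design and randomised.

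**2. How far the period contrast falls short of a contrast with no use**

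Let uM and uP be the shares of consultations held by telemedicine in telemedicine and telephone periods. Assume that savings are proportional to use. The period contrast reflects uM − uP, and telemedicine periods against no use reflect uM, so

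captured share = (uM − uP) / uM.

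All uptake values are assumptions. Section 5's figure of about 10% suggests a starting point for uP, but it refers to the most seriously ill children, including those with no consultation. The study includes only children who had one.

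| uP | uM | Captured share |
|---|---|---|
| 10% | 40% | 0.30 / 0.40 = 75% |
| 10% | 60% | 0.50 / 0.60 = 83% |
| 10% | 80% | 0.70 / 0.80 = 88% |
| 30% | 60% | 0.30 / 0.60 = 50% |

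Over a wider range, uP from 5% to 20% and uM from 30% to 90%, the share runs from 33% (0.10 / 0.30) to 94% (0.85 / 0.90). At uP = 0 it is 100%.

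**3. Direction of the error in the ratio**

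Let S be the saving and v the variable cost per telemedicine consultation, and F the fixed programme cost spread over all consultations. Assume S = 1000, v = 200, uM = 50% and uP = 10%.

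- A, programme against no programme: uM·S / (F + uM·v) = 500 / (F + 100).
- B, period saving over the period difference in cost: (uM − uP)·S / [(uM − uP)·v] = 400 / 80. F cancels.
- C, period saving over the full investment: (uM − uP)·S / (F + uM·v) = 400 / (F + 100).

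| F | A | B | C |
|---|---|---|---|
| 0 | 5.00 | 5.00 | 4.00 |
| 100 | 2.50 | 5.00 | 2.00 |
| 300 | 1.25 | 5.00 | 1.00 |

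With F = 100, one set of data gives 2.50, 5.00 or 2.00 per dollar. Against A, B is twice as large and C is 20% smaller. B is a valid answer to the randomised question, but it is not the return on having the programme.

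**The case against.** The strongest reply is that the disputed phrase is just loose wording for telephone consultation. The overall objective in section 4, the fourth aim, the Economic Evaluation paragraph and the hypothesis itself all set telemedicine against telephone, and a child who has only a telephone consultation is treated without telemedicine. Such children are in the study.

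That stands to this extent: a reader might infer that the trial never observes care without telemedicine, and the documents do not support that. Telephone-only care is observed at patient level. But modality received is then the physician's choice, and it is not the randomised contrast in the hypothesis. Reading the phrase as the telephone periods does not rescue it either, since telemedicine is permitted in them.

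A reader might also infer that the dollar means the full fixed investment, so that the return must be understated. The protocol defines the investment neither as fixed nor as incremental, and the analysis plan may settle the costing. Step 3 shows that the error can go either way. Nor can the shortfall be judged against telemedicine for every consultation: nobody proposes that, and that benchmark would exaggerate the loss.

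**Conclusion.** The point holds as a conflict over the comparator. The outcome definition names one comparator in its hypothesis and another in its result, and the assigned periods can deliver only the first. The period contrast compares two encouragement policies with telemedicine available under both. It matches a contrast with no telemedicine only if telephone-period use is zero, and it does not identify the return on having the programme.

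The size is unknown. The captured shares in step 2 rest on assumed uptake and on savings proportional to use. If physicians keep telemedicine in telephone periods for the children with most to gain, the true share would be smaller. The ratios in step 3 rest on invented costs and show only that the direction depends on the denominator. An analysis plan could define the costs, but the comparator conflict is in the protocol's own outcome text.

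**What to change.** 1. In the Economic Efficiency Cost-Analysis outcome, state the comparator as care in periods randomised to telephone, with telemedicine remaining available.
2. Take as the dollar the difference in telemedicine cost between the same assigned periods, so that numerator and denominator refer to one contrast.
3. Report telemedicine use by assigned period beside the ratio.
4. If a return for programme against no programme is still wanted, label it as modelled, and state the fixed cost and the no-programme scenario as assumptions.

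The cost is a change of wording and one added table. Section 12 already has consultation type abstracted and departures from assignment documented, so no new data are needed. The downside is a narrower economic claim.
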